### Setting and participants

Eligible participants are adults (≥ 20 years of age) who are scheduled to undergo open or laparoscopic or robot-assisted partial nephrectomy. We included patients with a normal contralateral renal function that will be confirmed as a preoperative split renal function of > 40% by the ^99m^Tc-DTPA radionuclide scintigraphy to compare the function of the kidney on the surgery.

Exclusion criteria are the patients with any of the following disease: clinically significant peripheral vascular disease affecting the upper arms, severe cardiopulmonary diseases (valvular or ischemic heart disease, heart failure, left ventricular ejection fraction < 40%, chronic obstructive pulmonary disease, forced expiratory volume in 1 s of < 40% of the predicted value), baseline chronic kidney disease (estimated GFR of < 30 ml per min per 1.73 m^2^ of body-surface area or preoperative serum creatinine level > 1.4 mg/dl), and hepatic failure (bilirubin level of > 1.2 mg/dl or international normalized ratio of > 2.0).

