### Study endpoints

The primary outcome is serum creatinine level 1 day after partial nephrectomy, as an index of postoperative kidney function. The secondary outcomes include the incidence of postoperative AKI and urinary biomarkers including urinary creatinine, microalbumin, β-2 microglobulin, and NAG measured immediately, and 1 day and 2 weeks after the partial nephrectomy (Fig. 2) [17–22]. The diagnosis of postoperative AKI will be based on the serum creatinine criteria of the Kidney Disease Improving Global Outcomes (KDIGO) criteria [26]. Estimated GFR (eGFR) measured immediately, and at 1 and 3 days, and 2 weeks after partial nephrectomy and renal rSO_2_ of the opposite kidney measured at 10-min intervals from the induction of anesthesia to the end of surgery will also be investigated as secondary outcomes. eGFRs will be calculated with the abbreviated isotope dilution mass spectrometry-Modification in Diet and Renal Disease Study equation, which is $$ \mathrm{eGFR}\ \left(\mathrm{ml}/\min /1.73\ {\mathrm{m}}^2\right)=175\times {\left(\mathrm{serum}\ \mathrm{creatinine}\right)}^{-1.154}\times {\left(\mathrm{age}\right)}^{-0.203}\times 0.742\ \left(\mathrm{if}\ \mathrm{female}\right)\times 1.212\ \left(\mathrm{if}\ \mathrm{black}\right) $$ [27].

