### Sample size

To determine the sample size, we reviewed serum creatinine changes in 20 patients who underwent partial nephrectomy. The mean value of serum creatinine was 1.60 mg/dl, and the standard deviation was 0.54 mg/dl at 1 day after partial nephrectomy. Assuming that the serum creatinine levels in the RIPC group were significantly lower than the levels in the control group by more than 0.35 mg/dl at 1 day after partial nephrectomy, 39 patients per group were required with a two-sided alpha-error of 0.05 and 80% power. Considering the 10% dropout rate, eight patients were added. The final sample size was determined to be 43 patients per group.

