### Statistical analysis

Data will be expressed as mean (standard deviation), median (interquartile range) or the number of patients (%). The normality of distribution of data will be tested by the Kolmogorov-Smirnov test. To compare the outcome variables and baseline characteristics between the RIPC and the control group, Student’s *t* test or the Mann Whitney *U* test will be used for continuous variables depending on the distribution of data and the chi-square test or Fisher’s exact test will be used for categorical variables depending on the expected counts. For the comparison of the time-dependent measurement of serum creatinine, eGFR, urinary biomarkers, and renal rSO_2_ of the opposite kidney, repeated measures analysis of variance will be used to assess the changes within and between groups over time. The presence and incidence of missing data will be reported. Multiple imputations using the Markov chain Monte Carlo algorithm will be performed for handling missing values in our study data. Multivariable logistic regression analysis will be performed to adjust for potential confounding factors known to affect the risk of AKI including surgical parameters shown in Table 1 and patient characteristics (age, sex, history of hypertension, diabetes mellitus, renal insufficiency, and congestive heart failure). We planned to perform subgroup analysis based on surgical modalities and R.E.N.A.L. nephrometry score.

Data will be analyzed using SPSS software (SPSS version 24.0, Chicago IL, USA). G*power (version 3.1.9.2, Universität Düsseldorf, Düsseldorf, Germany) was used to calculate the sample size. A *P* < 0.05 will be considered statistically significant. Bonferroni correction for multiple measurements will be used to reduce type 1 error.

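### Serial creatinine and eGFR would be better served by a baseline-adjusted mixed model than by the stated repeated measures ANOVA, whose uncorrected group-by-time test probably runs above 5% and has no stated way to combine over imputations

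*Protocol article*

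**What the plan says.** Under Statistical analysis, the protocol article states that for serial creatinine, eGFR, urinary biomarkers and renal oxygen saturation "repeated measures analysis of variance will be used to assess the changes within and between groups over time". The same section states that "Multiple imputations using the Markov chain Monte Carlo algorithm will be performed for handling missing values in our study data". It names no sphericity correction, multivariate test or covariance structure, and no rule for combining the ANOVA tests over imputations. SPSS 24.0 is the named software.

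The visits are set under Study endpoints: "Estimated GFR (eGFR) measured immediately, and at 1 and 3 days, and 2 weeks after partial nephrectomy". As eGFR is calculated from serum creatinine, creatinine follows the same schedule. Preoperative creatinine and eGFR are also collected (Data collection), which makes five occasions if the preoperative value is placed in the series.

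Two figures bear on the variances. Sample size reports for creatinine that "the standard deviation was 0.54 mg/dl at 1 day after partial nephrectomy". Setting and participants excludes patients with a "preoperative serum creatinine level > 1.4 mg/dl".

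**The concern.** The standard repeated measures F test for group-by-time holds its nominal level only under sphericity, meaning that the difference between any two visits has the same variance. Creatinine here starts from a restricted range, rises sharply after surgery and then recovers, at visits hours, days and then weeks apart. Equal variances of differences would be surprising.

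Two further features of the stated plan add to this. ANOVA needs complete rows and the plan fills them by multiple imputation, yet an omnibus F has no single estimate and standard error for Rubin's scalar rules to combine. And the preoperative value, which every patient must have to be judged eligible, is not used as a covariate. At stake are the error rate, precision and readability of the secondary longitudinal comparisons.

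**Working it through.** **The protocol's own figure.** With difference 0.35, SD 0.54 and 39 per group, the noncentrality is (0.35/0.54) × √(39/2) = 0.648 × 4.416 = 2.86. The exact t calculation gives 80.7% power, and 79.6% with 38. The stated 39 is reproduced. It concerns the single day-1 comparison, not the ANOVA.

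**What the eligibility cap shows.** The SD of a bounded variable is at most half its range. With the upper limit 1.4, the preoperative SD is at most (1.4 − 0)/2 = 0.70. If values start at 0.4 it is at most 0.50, and if at 0.5 at most 0.45 (lower limits assumed). The cap alone does not put the preoperative SD below 0.54.

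**What sphericity would require.** Var(Yj − Yk) = SDj² + SDk² − 2ρ·SDj·SDk must be the same for every pair of visits. Two assumed cases:

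- SDs 0.20 (preoperative), 0.30 (immediate), 0.54 (days 1 and 3), all ρ = 0.5. Preoperative to immediate: 0.04 + 0.09 − 0.06 = 0.07. Day 1 to day 3: 0.2916 + 0.2916 − 0.2916 = 0.29.
- SD 0.54 throughout, correlation 0.8 per visit step. Adjacent visits: 2 × 0.2916 × (1 − 0.8) = 0.117. Four steps apart: 2 × 0.2916 × (1 − 0.8⁴) = 0.344.

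The second case shows that serial correlation alone breaks sphericity, whatever the cap does to the preoperative SD.

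**Type I error of the group-by-time F test.** Simulation under no effect: 43 per group, five occasions, multivariate normal, 10,000 runs per pattern. Only the day-1 SD comes from the article. Epsilon = [tr(CΣC)]² / {(p − 1)·tr[(CΣC)²]}, with Σ the covariance matrix of the p visits and C the centring matrix; it equals 1 under sphericity.

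| SDs: preoperative, immediate, day 1, day 3, 2 weeks | Correlation | Epsilon | Uncorrected | Greenhouse-Geisser |
|---|---|---|---|---|
| 0.25, 0.30, 0.54, 0.45, 0.35 | equal 0.5 | 0.81 | 6.1% | 4.6% |
| same | 0.8 per step | 0.67 | 7.2% | 4.8% |
| 0.20, 0.30, 0.54, 0.54, 0.30 | equal 0.5 | 0.74 | 6.5% | 4.8% |
| same | 0.8 per step | 0.60 | 8.0% | 5.1% |
| 0.15, 0.20, 0.54, 0.40, 0.20 | equal 0.5 | 0.58 | 8.4% | 5.1% |
| same | equal 0.8 | 0.45 | 9.6% | 5.1% |
| 0.54 throughout | 0.8 per step | 0.63 | 8.0% | 5.2% |
| 0.54 throughout | equal 0.8 | 1.00 | 5.1% | 4.8% |

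With another assumed set (SDs 0.20, 0.25, 0.54, 0.50, 0.30; correlation 0.70 or 0.85 per step), the uncorrected error is 7.6% to 8.7% with five visits and 6.0% to 7.1% with the four postoperative visits only.

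**What the preoperative covariate is worth.** Same last set of SDs, 39 per group, assumed true differences 0.05, 0.35, 0.25 and 0.10 at the postoperative visits. The mean difference is 0.75/4 = 0.1875, or 0.75/5 = 0.15 if the preoperative visit (expected difference 0) is averaged in. Noncentrality = (difference/SD of the patient mean) × √(39/2). Adjusting for the preoperative value multiplies the SD by √(1 − r²), where r is its correlation with the postoperative mean.

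| | Correlation 0.70 per step | Correlation 0.85 per step |
|---|---|---|
| Five-visit mean, unadjusted | SD 0.291, noncentrality 2.28, power 61% | SD 0.323, 2.05, 53% |
| Four-visit mean, unadjusted | SD 0.336, 2.47, 68% | SD 0.366, 2.26, 61% |
| Four-visit mean, adjusted | r = 0.51, SD 0.289, 2.86, 81% | r = 0.73, SD 0.251, 3.30, 90% |

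**The case against.** The strongest defence is that the article names a family of tests and not its sphericity-assumed member. Epsilon-corrected and multivariate tests belong to repeated measures ANOVA and hold about 5%, and an analysis plan that is not shown may choose one. This stands: the inflation applies only if the F test is left uncorrected.

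A reader might infer that the method contradicts the trial's own figures. The documents do not support that. They give one creatinine SD, no between-visit correlation and no variance for eGFR, and the cap does not settle the preoperative SD. Failure of sphericity is likely, but it is inferred.

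A reader might also infer that the group-by-time result cannot be obtained after imputation. It can: multi-parameter combination rules exist, and any contrast with an estimate and standard error pools in the usual way. What is true is narrower: the omnibus F is not covered by the scalar rules and the article names no other route.

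The power gain must not be credited to dropping ANOVA as such. Leaving the preoperative visit out of the average gains 7 to 8 points (61% to 68%, 53% to 61%). The rest comes from the covariate, which an ANOVA could also carry. A Greenhouse-Geisser-corrected interaction test kept 88% to 94% power in one simulation under the same assumed effects.

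Finally, nothing says that within-group change will be read as benefit from preconditioning, and the t or Mann-Whitney tests also planned can give unadjusted comparisons at a visit.

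**Conclusion.** The point holds as a worthwhile improvement to a stated secondary analysis, not as an error in the primary one. The day-1 comparison and its 39 per group are untouched. If uncorrected, the group-by-time test for creatinine would run at about 6% to 9% in place of 5%, with 9.6% at the most uneven SDs tried and about 5% under equal SDs with equal correlations. These figures rest on assumed SDs at every visit but day 1, assumed correlations and normality. For eGFR the argument is by analogy only. The gain in power from 61%–68% to 81%–90% rests also on assumed effects at each visit.

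An epsilon correction would settle the error rate. It would not settle the pooling, the unused covariate or the lack of an adjusted effect estimate at each visit. A single replacement model settles all of these.

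**What to change.** For serial creatinine and eGFR, replace repeated measures ANOVA with a linear mixed model, which the named SPSS software can fit:

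- responses: the postoperative visits (immediate, day 1, day 3, 2 weeks);
- fixed effects: preoperative value, group, visit and group-by-visit;
- covariance: unstructured across visits;
- data: all observed visits, without imputing the outcome.

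Report the between-group difference with 95% CI at each visit, and keep within-group change descriptive.

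If ANOVA is kept, commit to the Greenhouse-Geisser-corrected test with the preoperative value as covariate, and name the rule for combining it over imputations.

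The cost is a change of analysis wording, slightly more modelling work and a degrees-of-freedom approximation for an unstructured covariance at 86 patients. No extra data are needed.

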### Data collection

Preoperative characteristics including age, sex, Body Mass Index, baseline values of serum creatinine concentration, eGFR, hemoglobin, ^99m^Tc-DTPA renal scintigraphy data, underlying diseases, medication status, smoking, and alcohol consumption will be collected.

We will collect surgery and anesthesia-related data including the R.E.N.A.L. nephrometry score [28], which are summarized in Table 1. Postoperative data will be assessed including the length of hospital stay, length of intensive care unit (ICU) stay, incidences of postoperative complications such as reoperation, postoperative wound infection, venous thromboembolism, myocardial infarction, and cerebrovascular accident.

**Table 1 Tab1:** Intraoperative data collection

Category	Variables
Surgery-related	Duration of surgery
	Type of partial nephrectomy (open/ laparoscopic/ robotic)
	Cold/warm ischemic
	Duration of renal ischemia
	Estimated blood loss
	R.E.N.A.L. nephrometry score
Anesthesia-related	Mean arterial pressure (lowest and highest)
	Total dose of anesthetics (propofol and remifentanil)
	Mean dose of anesthetics (sevoflurane or desflurane)
	Dose of vasopressors (ephedrine, phenylephrine, and calcium chloride)
	Dose of mannitol infused during surgery
	Urine output
	Total crystalloid/ colloid infused
	Blood transfusion amount
	Intraoperative complications

In our trial, all data will be entered electronically. Participant files are to be stored in numerical order and stored in an accessible and secure manner and place. Participant files will be maintained in storage for 3 years after completion of the study. Electronic data errors will be detected by programs designed to detect missing data or specific errors in the data.

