## Discussion

The present study will test the hypothesis that RIPC performed during partial nephrectomy will reduce the IRI caused by renal artery clamping during surgery as well as the surgical insult. Our primary outcome variable will be serum creatinine value measured on the first postoperative day. However, as serum creatinine may be non-specific and insensitive to detect early subclinical renal injury, urinary biomarkers, as well as other secondary clinical outcomes, will be compared between groups. Our study should be able to give a reliable answer to the question of whether RIPC could protect the kidney from IRI during partial nephrectomy.

Patients who undergo partial nephrectomy are prone to develop postoperative renal parenchymal injury theoretically. Only a few studies reported the incidence of AKI after partial nephrectomy with currently available criteria including RIFLE (risk, injury, failure, loss of function, end-stage renal disease), the Acute Kidney Injury Network (AKIN) or Kidney Disease Improving Global Outcomes (KDIGO). To our knowledge, in two previous studies investigating the development of AKI in patients who underwent partial nephrectomy, the incidences of AKI were reported as 39% and 54% according to AKIN and RIFLE criteria, respectively [14, 31]. Another retrospective study attempting to identify the predictors of 30-day AKI after radical or partial nephrectomy reported that the incidence of AKI, defined as an elevation of serum creatinine > 2 mg/dl above baseline or the need for dialysis, was only 1.8% [32]. This low incidence may be due to the different definition of AKI and different inclusion criteria. Our study will add data about the incidence of AKI defined by KDIGO criteria after partial nephrectomy.

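### The adjusted AKI model lists an excluded condition and variables known only after RIPC; at about 2.4 events per parameter its odds ratio would be unstable

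*Protocol article*

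**What the plan says.** The adjusted analysis of AKI is set out in the Statistical analysis section: "Multivariable logistic regression analysis will be performed to adjust for potential confounding factors known to affect the risk of AKI including surgical parameters" of Table 1, plus "patient characteristics (age, sex, history of hypertension, diabetes mellitus, renal insufficiency, and congestive heart failure". No limit on the number of terms and no selection rule is stated.

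The surgery-related rows of Table 1 (Data collection) are duration of surgery, "Type of partial nephrectomy (open/ laparoscopic/ robotic", cold or warm ischemia, "Duration of renal ischemia", "Estimated blood loss" and the R.E.N.A.L. nephrometry score. The Interventions section places RIPC after induction of anesthesia and before the renal artery is clamped.

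The exclusion criteria (Setting and participants) include "severe cardiopulmonary diseases (valvular or ischemic heart disease, heart failure, left ventricular ejection fraction < 40" among other conditions. They also exclude preoperative creatinine above 1.4 mg/dl.

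The same Statistical analysis section plans a chi-square or Fisher's exact test for categorical outcomes, which covers the unadjusted AKI comparison. The Discussion says that the sample size was set for day-1 creatinine and may be too small for AKI.

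**The concern.** Three features of the covariate list do not fit this trial.

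- **Heart failure.** It is both a reason for exclusion and a covariate. In the enrolled patients the column will be constant or nearly so, and its coefficient cannot be usefully estimated. Renal insufficiency is also restricted in range by the creatinine and eGFR limits.
- **Post-RIPC variables.** Duration of surgery, ischemia time and blood loss are called confounders, but they arise after the assigned treatment is given. Randomization already deals with confounding of assignment. Conditioning on what happens afterwards cannot improve on that, and it may change the effect being estimated.
- **Length.** The list is long for 86 patients and a binary outcome. Maximum-likelihood logistic regression with few events per parameter gives imprecise odds ratios that lie too far from 1 when there is an effect, with standard errors that are too small.

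AKI is the first secondary outcome named, and the limitations in the Discussion point to this multivariable adjustment. The admitted shortage of power warns a reader only about missing an effect. The overfitted model adds the opposite risk, an overstated one.

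**Working it through.** **The plan's own figures.** The protocol gives no event count or sample size for the AKI model. Its creatinine calculation reproduces: with a difference of 0.35, SD 0.54 and two-sided 0.05, power from the noncentral t is 0.796 at 38 per group and 0.807 at 39. Then 39 × 1.1 = 42.9, so 43 per group and 86 in total.

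**Parameters if all listed terms are entered.**

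| Source | Terms | Parameters |
|---|---|---|
| Arm | RIPC or control | 1 |
| Table 1, surgery-related | duration 1, type (three levels) 2, cold/warm 1, ischemia time 1, blood loss 1, R.E.N.A.L. score 1 | 7 |
| Patient characteristics | age, sex, hypertension, diabetes, renal insufficiency, heart failure | 6 |
| Total | | 14 (13 if heart failure is constant and drops out) |

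This reads surgical parameters as the surgery-related rows only. Adding the anesthesia-related rows would lengthen the list.

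**Events per parameter** = min(events, non-events) / parameters. The cited rates come from the Discussion: "the incidences of AKI were reported as 39% and 54% according to AKIN and RIFLE criteria". The trial uses KDIGO and assumes no rate of its own, so these are assumptions.

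- 39% in 86 patients: 0.39 × 86 = 33.5 events; 33.5/14 = 2.4, or 33.5/13 = 2.6.
- 39% in the 78 evaluable patients (2 × 39): 30.4 events; 30.4/14 = 2.2.
- 54% in 86: 46.4 events, so 39.6 non-events are limiting; 39.6/14 = 2.8.
- 25% in 86 (assumed): 21.5 events; 21.5/14 = 1.5.
- 39% in controls only and a true odds ratio of 0.50: the RIPC odds are 0.5 × 0.39/0.61 = 0.320, a risk of 0.242. Events = 43 × (0.39 + 0.242) = 27.2; 27.2/14 = 1.9.

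**Simulation of the consequence.** 86 patients, about 33 events, 2,000 runs per setting. Assumptions: independent covariates, six binary with 30% prevalence and the rest normal, each with a log odds ratio of 0.3 per SD. No covariate depends on RIPC.

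| Slopes | Median OR when the true OR is 0.50 | SD of log OR / median model SE (true OR 0.50) | Type I error at nominal 5% |
|---|---|---|---|
| 14 | exp(−0.872) = 0.42 | 0.73 / 0.63 | 7.7% |
| 13 | exp(−0.846) = 0.43 | 0.73 / 0.62 | 5.8% |

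On the log scale the estimates are too large by 0.872/0.693 − 1 = 26% and 0.846/0.693 − 1 = 22%. With no true effect the estimates centred on 1. Repeat simulations with 12 covariates plus arm put the median odds ratio at up to 0.44, and type I error across all runs was roughly 6 to 8%. The SD of the log odds ratio in those repeats was about 0.65, against 0.48 for arm plus two covariates. In one of them the short model had a median odds ratio of 0.51 and type I error of 5.2%.

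The unadjusted estimate has a median of exp(−0.57) = 0.57 and an SD of about 0.45. Its distance from 0.50 reflects the non-collapsibility of the odds ratio and is not an error. Nor does non-collapsibility explain the loss of precision: with 14 slopes the log odds ratio grows by 0.872/0.57 = 1.5, but its SD grows by 0.73/0.45 = 1.6.

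**With heart failure and the three post-RIPC variables removed, and nothing else.** Parameters: 1 + 2 + 1 + 1 + 5 = 10; 33.5/10 = 3.4. This is still sparse, so the list itself has to be shortened.

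**The case against.** The strongest defence is that this model is supportive. AKI will be compared directly by chi-square or Fisher's exact test, the primary outcome is day-1 creatinine, and the protocol already concedes limited power for AKI. All of that stands and limits the severity.

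A second defence is that the protocol does not say that all terms are entered together, and that coding or selection may be left to an analysis plan that is not shown. This is why the count of 14 is conditional. It does not rescue the list itself, which is printed and includes an excluded condition and post-RIPC measurements.

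A reader might infer that the adjusted odds ratio is bound to be biased. The documents do not support this.

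- Adjustment for post-RIPC variables distorts the effect mainly if RIPC alters them. No mechanism is given for a cuff on the arm to change clamp time or blood loss, surgeons are blinded, and the simulation gives no size for such bias.
- Type of surgery and R.E.N.A.L. score are essentially settled before surgery, and cold or warm ischemia is a blinded surgeon's choice of technique.
- Exaggeration from sparse data needs a true effect.
- A constant heart failure column simply drops out and leaves the RIPC odds ratio unchanged. Because the exclusion is framed as severe disease, a few milder cases may also remain.

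A reader might also expect frequent failures of the fit. That depends on how rare the binary covariates are, which the documents do not say. In the tabulated runs at most 0.1% of fits failed.

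**Conclusion.** The point holds as a should-fix matter for a secondary, supportive analysis. The covariate list contradicts the eligibility criteria on heart failure and treats at least three post-RIPC variables as confounders. Entered in full, it leaves about 2.4 events per parameter (1.5 to 2.8 across AKI rates of 25 to 54%). The adjusted RIPC odds ratio would then be unstable, overstated if RIPC works (about 0.42 to 0.44 for a true 0.50), and tested at roughly 6 to 8% instead of 5%. Bias from the post-RIPC variables is a risk only.

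The size rests on three assumptions: all listed terms are entered, the AKI rate is near the cited AKIN figure (which the Background presents as a high one), and covariate effects are of the simulated strength. The heart failure contradiction and the timing of the surgical variables rest on the text alone. The primary creatinine test, its sample size and the unadjusted AKI comparison are not affected.

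**What to change.** Reword the sentence on logistic regression as follows.

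- State that the unadjusted chi-square or Fisher comparison is the main analysis of AKI.
- Define one supportive logistic model with arm plus two or three pre-specified preoperative covariates, for example baseline creatinine or eGFR, R.E.N.A.L. score and, if wanted, the planned surgical approach. Arm plus two single-parameter covariates gives 33.5/3 = 11.2 events per parameter at 39%. Adding approach (two parameters) gives 33.5/5 = 6.7.
- Remove congestive heart failure and every variable measured after RIPC from the model. The eligibility criteria need no change for this purpose.
- Report the intraoperative variables descriptively by arm.
- Optionally, name penalised (Firth) likelihood as the fitting method in case of separation.

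The cost is one sentence and a shorter covariate list than advertised. Little power is lost: in one simulation at a true odds ratio of 0.50, power was 27% with the short model and 29% with the full one, and the latter is flattered by its excess type I error. Trial status reports 46 of 86 patients enrolled by June 2018. The change should be dated and made before allocation is disclosed.

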### Randomization and blinding

After the initial enrollment, participants will be randomly assigned in a 1:1 ratio to either the RIPC or the control group according to Internet-based computer-generated random numbers in block sizes of 4 or 6 (http://www.sealedenvelope.com). Group allocations will be concealed from the investigators using opaque envelopes. The random assignment will be conducted by a third party independent of the study, and the assignment records will not be disclosed until the end of the study. On the day of the surgery, the opaque envelope containing the group allocation will be delivered to an anesthesiologist who is not involved in the study and is responsible for patient care and the RIPC intervention. Participants, urologic surgeons, post-anesthesia care staff, data collectors, and investigators assessing outcome data will be blinded to the treatment allocation to minimize potential sources of bias.

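### Plain Bonferroni for the repeated secondary measurements is valid, but Holm's step-down version gives the same 5% guarantee and never rejects less: a cheap, optional improvement

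*Protocol article*

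**What the plan says.** The Statistical analysis section assigns the series measured over time (serum creatinine, eGFR, urinary biomarkers, renal rSO2) to repeated measures ANOVA. It sets the significance level ("A *P* < 0.05 will be considered statistically significant") and adds: "Bonferroni correction for multiple measurements will be used to reduce type 1 error". It does not say which comparisons form the family or how many there are.

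Under Study endpoints, the primary outcome is serum creatinine at a single time, day 1. The secondary urinary biomarkers are taken at three postoperative times (immediately, day 1, 2 weeks). The secondary eGFR is "measured immediately, and at 1 and 3 days, and 2 weeks after partial nephrectomy", which is four times.

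The Sample size section sizes only the day-1 creatinine comparison: "39 patients per group were required with a two-sided alpha-error of 0.05 and 80% power".

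**The concern.** If the correction is applied to group comparisons at each time, plain Bonferroni holds every p-value to 0.05/k, where k is the number of times. Holm holds only the smallest p-value to 0.05/k. It then relaxes the threshold step by step to 0.05/(k-1), 0.05/(k-2) and so on, and stops at the first failure. Both keep the family-wise error at or below 5% whatever the correlation between times. Anything Bonferroni rejects, Holm rejects too.

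What is at stake is power in the secondary series. The Discussion relies on the urinary biomarkers because creatinine may miss early injury. If a difference persists over several visits, Bonferroni may declare it at fewer of them than the same error guarantee allows.

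**Working it through.** **Inputs from the protocol.** Difference 0.35 mg/dl ("lower than the levels in the control group by more than 0.35 mg/dl at 1 day after partial nephrectomy"); SD 0.54 ("the standard deviation was 0.54 mg/dl at 1 day after partial nephrectomy"); 39 evaluable patients per group; 1:1 allocation; two-sided 0.05; k = 3 (biomarkers) or k = 4 (eGFR).

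**Inputs assumed.** The standardised effect d = 0.35/0.54 = 0.648 is borrowed from day-1 creatinine and applied to secondary outcomes at other times. The within-patient correlation is set to 0.3 and 0.6.

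**1. The plan's own figure.** For a two-sample t test the noncentrality is d × √(n/2). At n = 39 this is 0.648 × √19.5 = 2.86. Power is 79.6% at n = 38 and 80.7% at n = 39, so the stated 39 reproduces. The dropout step ("Considering the 10% dropout rate, eight patients were added") gives 2 × 39 + 8 = 86, or 43 per group. This is one test at 0.05, and no multiplicity correction enters it.

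**2. Bonferroni does what the protocol asks.** Under independence the family-wise error is 1 − (1 − 0.05/k)^k:
- k = 3: 1 − (1 − 0.0167)³ = 0.0492
- k = 4: 1 − (1 − 0.0125)⁴ = 0.0491

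Correlation lowers it further. In simulation with no effect at any time, it was 4.8% at correlation 0.3 and 4.1% to 4.2% at 0.6. Holm was identical, because the first step of the two methods is the same.

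**3. Power of one comparison under Bonferroni.** The same t test at n = 39 has power 66.1% at 0.05/3 and 62.0% at 0.05/4.

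**4. Bonferroni against Holm.** Simulated two-sample t tests, 39 per arm, 40,000 trials per scenario. Entries are average power per time point that has an effect.

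| Times | Effect at | Correlation | Bonferroni | Holm | Gain (points) |
|---|---|---|---|---|---|
| 3 | 1 | 0.3 | 66.0% | 66.2% | 0.2 |
| 3 | 1 | 0.6 | 66.0% | 66.0% | 0.1 |
| 3 | all 3 | 0.3 | 66.2% | 74.9% | 8.7 |
| 3 | all 3 | 0.6 | 66.0% | 73.7% | 7.7 |
| 4 | 1 | 0.3 | 62.1% | 62.2% | 0.1 |
| 4 | 1 | 0.6 | 62.2% | 62.2% | 0.0 |
| 4 | 2 | 0.6 | 62.2% | 64.5% | 2.3 |
| 4 | all 4 | 0.3 | 62.0% | 72.2% | 10.1 |
| 4 | all 4 | 0.6 | 62.1% | 71.2% | 9.1 |

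Gains were taken before rounding. A separate z-test simulation over correlations 0 to 0.8 gave gains of 6 to 11 points when all times had the effect.

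**5. Where the methods do not differ.** The chance of at least one rejection was the same under both in every scenario. Holm gains only from the second rejection onward.

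**The case against.** The strongest objection is that nothing here is wrong. The protocol says that Bonferroni will reduce type I error, and it does. The choice is pre-specified and conservative, comes with simple simultaneous confidence intervals, and is nowhere claimed to be the most powerful. All of this stands, and an investigator who wants matching intervals has a legitimate reason to keep it.

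A reader might infer more than the document supports:

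- **That Holm has higher power in every case.** It is never lower. With an effect at one time only, it is practically equal.
- **That Bonferroni buys no protection at all.** The guaranteed bound is the same, but realised error can differ. With effects at two of four times and correlation 0.6, false rejection at the other two occurred in 2.3% of simulated trials under Bonferroni and 3.6% under Holm. Both are below 5%.
- **That the largest gains are to be expected here.** The protocol gives no effect size, SD or correlation for eGFR or any biomarker. With an equal effect at all four times and correlation 0.6, the chance of rejecting at every one rises from 35% to 56%. However, the protocol does not make that a criterion of success.
- **That the secondary series are known to lack power.** The only power limitation stated in the Discussion concerns AKI incidence, a binary outcome outside these series.
- **That every time point is certainly tested at 0.05/k.** The text defines neither k nor the family. That detail may stand in a full protocol or analysis plan not shown, so its absence is no finding.
- **That the main result is affected.** The primary outcome is one comparison at one time.

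**Conclusion.** The point holds as a low-priority improvement and not as the correction of an error. For follow-up group comparisons at single time points, Holm is at least as good as plain Bonferroni on adjusted p-values. Its benefit runs from about nil (effect at one time) through about 2 points (two of four times) to about 8 to 10 points per time point (equal effect at all times). The upper end rests on d = 0.648 throughout and a correlation of 0.3 to 0.6, both assumed. The size also presumes that the correction is applied across time points within one outcome. The day-1 creatinine test, the 39 and 43 patients per group, and the overall ANOVA tests stay as they are.

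**What to change.** Before unblinding, replace the Bonferroni sentence for the secondary series with wording such as:

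> *Within each secondary outcome, p-values for between-group comparisons across time points will be adjusted by the Holm step-down procedure (family-wise 0.05).*

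This needs no new data and no change to the sample size. The adjusted values follow directly from the ordered unadjusted p-values.

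The cost is in the intervals, because Holm has no equally simple simultaneous ones. Report them as unadjusted 95% intervals or as Bonferroni-adjusted intervals, and label which. With unadjusted intervals, an interval can exclude zero while its Holm-adjusted p-value exceeds 0.05. With Bonferroni-adjusted intervals, the reverse can occur. If matching intervals matter more to the investigators than the possible gain in power, keeping Bonferroni is defensible.
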